### AIM Intervention

#### Overview

After completing a recent systematic review focused on the IPV interventions relevant to women during the COVID-19 pandemic, including research evidence from 4 systematic reviews and 20 individual studies [27], our team identified an advocacy health promotion program [34] that was ideal to adapt, implement, and test in this RCT. Given that the advocacy health promotion program is not a proprietary program, permission was not required to adapt it for our research. The intervention reported by Tiwari et al [34] has been selected to be adapted for this trial because the researchers reported that it significantly reduced depression and psychological aggression scores and improved perceived social support and the use of safety-promoting behaviors. Other interventions that we examined in our systematic review either did not result in positive outcomes for the health and safety needs of women or the results did not reach statistical significance. We also found that providing highly tailored interventions can contribute to positive outcomes [35,36], and the intervention reported by Tiwari et al [34] could be tailored as needed. This study will pay particular attention to ensuring that those who are trained to deliver the intervention provide individualized and person-centered support.

An innovative aspect of this research is the adaptation of the intervention to meet the needs of midlife and older women that can often be different from those of younger women. For example, leaving one’s home, property, and community may not be a priority for older women experiencing IPV [19], and therefore, the women will be provided support to empower them to identify their own goals and strategies for achieving those goals. The intervention has also been adapted to meet the needs of women who reside in the Maritime provinces of Canada. Information on local IPV services and resources will be provided to the participants. The format will also be adapted to meet the preferences of the women to use whatever form of technology they prefer for the social support component of the study. In addition, those trained to deliver the program will use a person-centered perspective to support the unique needs of the participants, such as for participants who are francophone, living in a rural place, or a new immigrant to Canada.

We have chosen to name the program the Advocacy Intervention for Women in Midlife and Older, and we will use the acronym AIM to refer to the intervention. The AIM intervention has 2 components: an empowerment component and a social support component. These components are theoretically congruous with the framework we are using based on the empowerment model by Dutton [37] and the social support theory by Cohen [38]. We expect that the combination of the empowerment and social support components will be highly effective.

#### Components of AIM

The empowerment component is derived from the empowerment model by Dutton [37] to increase women’s safety. This component will involve the facilitator providing a 1-hour-long individual one-on-one information-sharing session with the participants that will be delivered virtually by telephone or video call. These sessions will include providing information on recognizing increased danger and how to use an individualized safety plan adapted for older women, providing information about cycles of violence, providing community and legal resources, and developing goals and strategies for the future. In addition to discussing this information, print materials will be provided electronically (via email) or in hard copy (via postal mail). Thus, this component clearly contributes to awareness raising and also empowers the women to develop changes in the future.

The social support component is based on the social support theory by Cohen [38] that involves tangible and perceived social support to contribute to health and well-being. This component will involve the facilitator scheduling weekly telephone or video calls over a course of 12 weeks at a time that is convenient to the participant. The duration of calls is variable and would average approximately 20 minutes per call. The calls are intended to provide encouragement and support and to answer questions the participant may have about using or applying the resources provided in the empowerment component. There are no specific or scheduled topics that are planned for each session. These are very individualized and based on the women’s needs and questions that each woman may wish to discuss. For example, facilitators will be prepared to help women with recognizing their past abuse and processing the abuse as well as providing support to women who are undergoing court proceedings and legal issues. The social support provided through the weekly contact is a key component of the intervention in addition to the topics discussed.

#### Comparison Group

The comparison group will receive a static, nontailored version of the AIM intervention materials after baseline data collection. They will be asked if they prefer to receive these materials via email or postal mail. The document will include a condensed version of the empowerment component and information about the dynamics of abusive relationship, warning signs of abuse for older adults, materials on safety planning and digital safety, local and national IPV resources, and guidance for setting goals for the future. The participants in the comparison group will not receive any further contact from the research team or facilitators to discuss these materials. Textbox 1 outlines the features (ie, information and support) that participants will receive depending on what group they are randomly assigned to.

Features of the advocacy intervention for midlife and older women (AIM) intervention group and comparison group.
**AIM intervention group**
Receives the information packageParticipates in 1-hour-long information-sharing session with the program facilitatorParticipates in 12 weekly social support sessions with the program facilitator
**Comparison group**
Receives the information package

### Sample Size

For the quantitative portion of the study (ie, the RCT), we determined an appropriate sample size that would be sufficient to contribute to the evidence base. We reviewed the sample sizes analyzed in the systematic review we conducted, the sample sizes of the studies focused on women experiencing IPV in midlife and older, and the sample size calculations in the study from which we have adapted the program [34]. We used our prior experience in recruiting midlife and older women as well as the resources available to conduct this research. We then concluded that recruiting 30 participants per arm is sufficient, that is, 30 women randomized into the intervention arm and 30 women randomized into the control arm. To account for a 15% attrition rate identified in a similar study [39], we will recruit 70 women, with 35 randomized to each group.

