### Participant Involvement by Group

Participant recruitment began in October 2023 and is expected to continue until July 2024. Participants will complete the screening and informed consent process with research staff and will be randomized upon completion of their baseline surveys. Participants that have been randomized to the intervention group will be matched with a facilitator in their region. The facilitators will follow up after randomization and schedule the 1-hour-long information-sharing session (ie, empowerment component) and then continue to follow up with the weekly calls for 12 weeks (ie, social support component). Quantitative survey data will be collected from all the participants at 3- and 9-month follow-ups. Follow-ups with participants in the AIM intervention group will take place 3 and 9 months after their final social support session. For participants randomized to the comparison group, follow-ups will take place 3 and 9 months after they have completed the baseline surveys. We estimate the total time commitment for participants to be 11 hours for those randomized to the AIM intervention group and 4 hours for those in the comparison group. Table 2 breaks down the estimated time commitment for each study activity.

**Table 2 table2:** Participant involvement by group.

Study activity	Time commitment for participants in the AIM^a^ intervention group (hours)	Time commitment for participants in the comparison group (hours)
Informed consent process	0.5	0.5
Baseline data collection	1.5	1.5
Empowerment component	1	—^b^
Social support component	6	—
3-month follow-up	1	1
9-month follow-up	1	1
Total time commitment	11	4

^a^AIM: advocacy intervention for midlife and older women.

^b^Did not participate.

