### Statistical Analysis

Quantitative data will be exported from REDCap as a spreadsheet and then uploaded into SPSS (IBM Corp) for quantitative analysis. Participants in the AIM intervention group need to complete the empowerment component and attend at least 10 out of 12 weekly calls of the social support component for their quantitative data to be included in the analysis.

Descriptive statistics will provide a profile of study participants, including demographics for the whole sample and for those in each of the 2 groups. The provisional effect of the intervention will be tested using a prospective chi-square test of independence between the 2 groups for categorical data (Fisher exact test) at 3 and 9 months. Repeated measures analysis of variance will measure mean differences between the groups on continuous variables at 3 and 9 months.

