### Qualitative Component

We will conduct interviews with approximately 12 participants of the AIM intervention group. This sample size is sufficient when using a qualitative descriptive approach to generate rich, detailed descriptions and meaningful data [49,50]. In these interviews, we will use maximum variation sampling to include women who have specific characteristics (eg, francophone, new immigrant, and rural) and ask them about their perceptions of the program and their recommendations for further program development. We will also invite any intervention group participants who did not complete the AIM program to participate in an interview to learn about their experiences in the program and ask for any recommendations they may have to help improve the program. All facilitators who deliver the AIM intervention to trial participants will be invited by telephone or email by the research coordinator to complete a qualitative interview. While all will be invited, we hope that at least 4 to 5 will volunteer to participate in the interview.

At the 9-month follow-up data collection point, the research coordinator will invite women from the AIM intervention group to take part in a virtual interview. To be eligible to be invited for the interview, participants must have completed the empowerment component and at least 10 out of 12 social support sessions. In these interviews, the research coordinator will try to recruit a diverse sample of women who represent the characteristics of the participants and ask them about their perceptions of the program and their recommendations for further refinement of the program to meet the needs of diverse midlife and older women. The informed consent form will be shared by email or by postal mail.

The research team will also conduct an exploratory qualitative analysis on the data recorded by the program facilitators. Facilitators will be instructed to record the date and length of each session and take notes. The notes will detail the topics discussed with participants, the support and resources offered to participants, and any questions or concerns raised by the participants. The analysis of this exploratory data will summarize what topics are discussed and what supports are provided to participants.

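### The 35 per arm allows for 15% attrition only, but the analysis also drops AIM women who miss the programme-completion rule, so 30 analysed AIM women are not secured

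*Protocol article*

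**What the plan says.** Two sections of the protocol article bear on how many women are analysed.

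- **Sample Size.** The target is set first: "We then concluded that recruiting 30 participants per arm is sufficient, that is, 30 women randomized into the intervention arm", and likewise 30 in the control arm. It is then raised for one loss: "To account for a 15% attrition rate identified in a similar study [39], we will recruit 70 women, with 35 randomized to each group". The allowance is the same in both arms. The 30 rests on the sizes of other studies, the calculations in the study from which the programme was adapted, and practical grounds: "We used our prior experience in recruiting midlife and older women as well as the resources available to conduct this research". The section states no significance level, power, effect size or standard deviation of its own.
- **Statistical Analysis.** Inclusion in the AIM arm has two conditions: "Participants in the AIM intervention group need to complete the empowerment component", and they must "attend at least 10 out of 12 weekly calls of the social support component for their quantitative data to be included in the analysis". Nothing comparable applies to the comparison arm.

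Two other sections give context. Participant Involvement by Group plans the 3- and 9-month surveys for every participant. Qualitative Component foresees women who stop the programme but can still be reached: "We will also invite any intervention group participants who did not complete the AIM program to participate in an interview".

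**The concern.** Inflating a target for attrition makes sense only if the target is the number wanted after losses. Read that way, the Sample Size section plans for about 30 women per arm with usable data, and the only loss it plans for is attrition. The Statistical Analysis section then removes a second group: AIM women who stayed in the study but did not complete enough of the programme. No allowance is made for them, and they come from one arm only.

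Thirty per arm is the only size the article calls sufficient. If it is not secured in the arm under test, the arms are likely to be unequal at analysis, and a reader who takes 30 v 30 from the Sample Size section would expect more precision than the analysis may have. The point here is the count. Whether a one-arm exclusion made after randomisation biases the comparison is a separate question.

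**Working it through.** **Inputs from the article:** target 30 per arm; attrition 15%; 35 randomised per arm; AIM-only inclusion rule (empowerment component plus at least 10 of 12 calls).

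**Input not in the article:** the share *a* of retained AIM women who meet the rule. It is assumed below over a range.

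**1. Reproduce the stated figure.** 30 x 1.15 = 34.5, which gives 35 per arm and 70 in total. Dividing instead, 30/0.85 = 35.3. Checking back, 35 x 0.85 = 29.75, about 30. So 35 is a reasonable answer for attrition alone. The 30 itself cannot be reproduced, because no design parameters are stated.

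**2. Room left for the second loss.** To keep 30 of 35, at most 5 women may be lost for all reasons, and 5/35 = 14.3%. The planned attrition alone is 0.15 x 35 = 5.25 women. Nothing is left over for the inclusion rule.

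**3. Expected AIM number after both losses.** Expected number = 35 x 0.85 x *a*. Number to randomise to AIM for 30 expected = 30/(0.85 x *a*), rounded up. The last column is the exact binomial chance that at least 30 of 35 are analysable, with per-woman probability 0.85 x *a*.

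| Assumed *a* | Expected AIM analysed | AIM randomised needed for 30 | Chance of at least 30 of 35 |
|---|---|---|---|
| 100% | 29.75 | 36 | 0.57 |
| 90% | 26.8 | 40 | 0.14 |
| 80% | 23.8 | 45 | 0.015 |
| 70% | 20.8 | 51 | 0.001 |
| 60% | 17.9 | 59 | below 0.001 |

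The comparison arm stays at 29.75 expected throughout.

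**4. Precision, as illustration only.** With equal standard deviations, the standard error of the group difference relative to 30 v 30 is sqrt[(1/n + 1/30)/(2/30)]. For n = 27, 24, 21 and 18 this is 1.03, 1.06, 1.10 and 1.15. Under a normal approximation with two-sided 5% and 80% power, neither of which the article states, the detectable standardised difference is (1.96 + 0.84) x sqrt(1/n + 1/30). It is 0.72 for 30 v 30, and 0.74, 0.77, 0.80 and 0.84 for those n.

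**The case against.** The strongest reply is that the Sample Size section never states an analysable number. It speaks of women randomised, and it does not say what the 15% counts. The rate comes from a cited study, and if it includes women who dropped the programme, part or all of the second loss is already covered. Women who miss three or more calls may also be largely the same women who are lost to follow-up. Calls are arranged at the participant's convenience, so adherence may be high; at 90% the standard error rises by only about 3%. And as the 30 rests on no stated power, no power loss can be derived from the article.

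Most of this stands, and it limits the point in three ways.

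- A reader might infer that the AIM arm will fall below 30. The article does not support that as a fact: the shortfall depends on an adherence rate it does not give and on a definition of attrition it does not give.
- A reader might infer an arithmetic error in the 35. There is none; it follows from 30 and 15%.
- A reader might infer that a planned power is lost. No power is planned, so step 4 above only illustrates scale.

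What the reply does not remove is the mismatch. Nothing in the article says that the 15% covers programme non-completion. It is applied equally to both arms, although only one arm has a programme to complete. The plan to interview non-completers shows that women who stop the programme but remain reachable are expected. If the 15% was meant to include them, the text should say so.

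**Conclusion.** The point holds as an inconsistency between the Sample Size and Statistical Analysis sections. The allowance covers one loss, equal in both arms, while the analysis applies a second loss in the AIM arm only. Unless the 15% already includes programme non-completion, the 30 called sufficient is not secured there, and the expected AIM number falls further below 30 as soon as any retained woman is expected to miss the rule.

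The size depends on adherence. Over an assumed 90% to 60% among retained women, about 27 down to 18 AIM women would be analysed, against about 30 in the comparison arm. This takes 15% attrition in each arm and treats the rule as a loss on top of it; overlap between the two would reduce the shortfall. The matter is worth correcting because 30 per arm is the only size the article defends and the correction is cheap.

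**What to change.** Keep 70 randomised and make both sections refer to one population.

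- **Preferred.** In Statistical Analysis, make the main analysis all women with follow-up data, each in the arm to which she was randomised, and report the set meeting the empowerment and 10-of-12 conditions as a secondary analysis. This matches what 35 per arm with 15% attrition provides, about 30 per arm. It also takes the one-arm exclusion out of the main comparison. It needs no extra participants, since the follow-up surveys are already planned for everyone. One detail should be settled at the same time. The article says "Follow-ups with participants in the AIM intervention group will take place 3 and 9 months after their final social support session", so it should state how those dates are fixed for a woman who stops the calls early.
- **Fallback.** If the 10-of-12 set remains the main analysis set, say in Sample Size that the 15% does not cover this exclusion and that fewer than 30 AIM women are expected. Give the expected number with the sponsor's own adherence assumption, and label any precision figure as an illustration. If the 15% was in fact meant to cover non-completion, say that instead and explain why the same rate applies to the comparison arm.

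Either change costs a few sentences. Under the preferred one, the main result describes women as assigned rather than women who completed the programme. Under the fallback, the stated AIM number becomes less favourable.

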### Participant Recruitment

The facilitators were asked to recruit participants within their organization. Facilitators were encouraged to distribute the recruitment poster for the study to potentially eligible participants in the following formats: (1) through email, phone call, social media (eg, Facebook), or in-person visit or (2) through a poster placed in a central location (eg, a lobby of a building) or a handout given to potential participants. Potentially eligible women will be assured that choosing not to participate in the study will not negatively affect their access to other services. They will be asked whether they are comfortable with the facilitator providing the research team with their names and contact information, or alternatively, whether they would prefer to contact the research team on their own. Facilitators were asked to distribute the study’s recruitment poster throughout their region. This included sending email requests to organizations and distributing the poster to community bulletin boards.

Once a potential participant reaches out to the research team by phone or email or is referred by a facilitator, research staff (eg, research coordinator or research assistant) will respond and arrange a time to communicate with them by telephone. Research staff will provide an overview of the study details with each potential participant and answer any questions they have, ensure that they meet the study inclusion criteria, and review the informed consent forms. Once these first steps are complete, the research team will contact the participant to schedule a time to collect the baseline survey data.

We will include any woman who fulfills the eligibility criteria, and there are no quotas for women with specific characteristics, but we will try to include women from diverse backgrounds, including francophone women, new immigrants, women from visible and racialized minority groups, women living in rural places with limited access to services, and women in same-sex relationships. We will try to recruit women from diverse backgrounds by contacting organizations that offer services to women from marginalized or diverse backgrounds in the Maritime provinces and asking them to take part in a research partnership. Given that the professionals working in these organizations (eg, transition houses, outreach programs, and women’s centers) have the expertise in working with these populations, they will be instrumental in helping us to reach and recruit diverse women into the study. In this study, our definition of rural is informed by the rural and small-town definition, which includes towns with population <10,000 inhabitants and people who live outside the commuting zone of a large urban center (eg, >40 minutes) [40,41].

### Partnerships With Community-Based Organizations

#### Overview

The facilitators were recruited by the research coordinator with the support of the study coinvestigators and study partners. The study team developed a contact list of potential organizations throughout the Maritime provinces that deliver services for older adults experiencing abuse and those who work with women experiencing IPV. The organizations included transition houses, IPV outreach services, women’s shelters, women’s centers, and other service providers for women (eg, sexual health centers and addiction services). The research coordinator contacted the organizations via email to inquire about forming a partnership with the research team. The organizations were asked if they would be willing to collaborate with the study team by agreeing to 1 of the 2 research partnerships we offered. Organizations that expressed interest in partnering upon our initial email were requested to meet with the research team virtually to discuss the study and answer any questions.

#### Partnership 1

Organizations were asked if they would be interested in partnering with the study by appointing a staff member who could serve as a facilitator on the project. Organizations were notified that the facilitators would need to take part in a 2-hour training session on how to deliver the intervention and would be assigned the tasks of recruiting potential participants and delivering the intervention to any participants that they recruited within their organization. Organizations were informed that they would receive a stipend of CAD $2500 (CAD $1=US $0.74) for agreeing to partnership 1 and having a staff member take part in the training and recruiting and delivering the intervention to 1 to 5 participants. An additional CAD $2500 stipend will be offered to any organization that has a facilitator who recruits and delivers the intervention to ≥6 participants, given the increased time and resources this would take. A technology fee of CAD $1000 will be provided to each partnering organization for overhead costs and the use of their equipment (ie, laptops and phones) to deliver the intervention. Organizations were notified that staff members need to meet the following criteria to be eligible to become a facilitator: (1) at least 2 years of experience working in the IPV service delivery field and (2) completion of a postsecondary education program (eg, social work, health professions, human services, counseling, health promotion, or social sciences).

The research team also hired staff facilitators throughout the Maritime provinces to deliver the intervention to participants that were not recruited from within community-based organizations. The staff facilitators will be completing the same tasks but will be working independently (ie, not with an organization). All staff facilitators need to meet the minimum educational and experience requirements.

#### Partnership 2

We offered a CAD $500 honorarium to organizations that were willing to help us out with participant recruitment only. The research team asked partnering organizations if they could help with recruitment by distributing the recruitment poster to potential participants and completing 1 of the following tasks: (1) asking potential participants within their organizations for permission for a member of the research team to contact them and (2) share information about the study with potential participants who can contact the research team directly if they wish to do so.

